### Data Collection

#### Focus Groups

The topic of the interviews are focused on patients’ experiences with the traumatic event (see Study Procedures). In addition, participants were asked to complete socio-demographic questions, the IES-R and the HADS. All focus groups have the same structure and are audio-recorded. The recorded focus groups are transcribed verbatim [26,27].

In case of observed severe symptoms of ASD or PTSD during focus group sessions, the treating physician was informed. The doctor could refer the patient for a consult with a psychologist in the department of Medical Psychology at the Elisabeth-TweeSteden Hospital who is specialized in psychological treatment after injury.

#### Observational Study

Data for the observational study will be collected using a structured interview—MINI-plus for ASD and PTSD—as well as self-report questionnaires: (1) the IES-R for ASD and PTSD, (2) HADS, (3) NEO Five-Factor Inventory (NEO-FFI) and the State Trait Anxiety Inventory (STAI) - Trait scale for personality, and (4) World Health Organization Quality of Life assessment instrument-Bref (WHOQOL-Bref) for QOL. All outcome measures will be assessed after treatment in the shock room (baseline), 3, 6, 9, and 12 months after injury. However, ASD and personality will only be measured at baseline (see Table 1).

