**Objective:**

The aims of this multi-method study are to explore patients’ experiences with injury (and their care) using a focus group study. Then, in the observational study, different courses of ASD, PTSD, and quality of life will be examined. In addition, this study will examine if these courses could be characterized by socio-demographic, clinical, and psychological variables. Consequently, a risk profile will be developed to determine which patients are at risk for developing ASD or PTSD during the 12 months after injury.

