## Introduction

Due to registration and implementation of specialized trauma care, the quality of medical treatment has been improved and survivorship has been increased [1-6]. Trauma is related to physical disabilities (eg, pain, fatigue and impaired wound healing), acute stress disorder (ASD), posttraumatic stress disorder (PTSD), and psychological distress [7-13]. Moreover, trauma patients experience an impaired quality of life (QOL) compared to the general population [14-20].

About 25% of trauma patients have subsyndromal ASD during hospitalization and about 30% had PTSD one month after injury [8,21]. Six months after injury, 49% showed a delayed onset of PTSD. This percentage decreased to 20% at 24 months after injury. A recent systematic review showed that patients diagnosed with ASD had a higher risk of developing PTSD [8]. However, the prevalence rate of patients with ASD who develop PTSD is unknown. Diagnostic criteria for ASD and PTSD are similar; however, dissociative symptoms (eg, depersonalization, derealization, and dissociative amnesia) are only emphasized in ASD and not in PTSD. Moreover, ASD can only be diagnosed within the first month after trauma and last for less than a month, while PTSD symptoms persist for at least one month after injury [22]. PTSD symptoms may begin either after trauma or months or years afterwards [23].

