This multi-method study consists of a focus group study and an observational prospective study. The ultimate goal of this multi-method study is to provide valuable insight into the severity of psychological consequences, including ASD and PTSD, and the need for a psychological intervention study to prevent PTSD. First, focus groups are held to examine patients’ experiences with injury (and their care). In this way, potential factors related to the development of psychological problems (eg, depressive symptoms) and disorders (eg, anxiety, ASD, and PTSD) can be obtained and taken into account for the observational study (aim 1). Subsequently, an aim of the observational study is to examine the courses of ASD and PTSD (aim 2). In addition, it will be examined which socio-demographic (ie, sex, age, marital status, and education level), clinical (ie, type of trauma, Injury Severity Score (ISS), Glasgow Coma Score, being hospitalized, being treated on the intensive care unit, complications during treatment, and treatment by a medical psychologist or psychiatrist), and psychological variables (eg, anxiety, depressive symptoms, and personality) characterize the courses of ASD and PTSD. Subsequently, a risk profile will be developed to determine which patients are at risk for ASD and/or PTSD (aim 3). Finally, to study the effect(s) of the natural course of ASD symptoms on the development of PTSD, anxiety and depressive symptoms, and QOL across time will be analyzed (aim 4).

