**Observational study**				
	MINI-Plus	ASD^e^ PTSD	Primary outcome	Baseline 3 months 6 months 9 months 12 months
	IES-R	ASD PTSD	Primary outcome	Baseline 3 months 6 months 9 months 12 months
	HADS	Anxiety Depressive symptoms	Secondary outcome	Baseline 3 months 6 months 9 months 12 months
	NEO-FFI^f^	Personality	Secondary outcome	Baseline
	STAI^g^-Trait	Personality	Secondary outcome	Baseline
	WHOQOL-Bref^h^	QOL^i^	Secondary outcome	Baseline 3 months 6 months 9 months 12 months

^a^N/A: Not applicable.

^b^IES-R: Impact of Event Scale-Revised.

^c^PTSD: posttraumatic stress disorder.

^d^HADS: Hospital Anxiety and Depression Scale.

^e^ASD: acute stress disorder.

^f^NEO-FFI: NEO Five-Factor Inventory.

^g^STAI: State Trait Anxiety Inventory.

^h^WHOQOL-Bref: World Health Organization Quality of Life assessment instrument-Bref.

^i^QOL: quality of life.

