#### Observational Study

The patient characteristic will be studied using descriptive statistics. Then, the baseline characteristics (ie, sociodemographic, clinical, and psychological variables) of participants versus nonparticipants, participants who complete versus drop out during follow-up, and participants who are discharged versus being in the hospital after treatment in the shock room will be compared using independent t-tests and Chi-squared tests. Nonnormal continuous data will be analyzed with Mann-Whitney U tests or Fisher’s exact tests.

Repeated measures of latent class analysis will be used to analyze the courses (ie, time is independent variable) of ASD and PTSD (dependent variables). Moreover, to examine if these different courses of ASD and PTSD (independent variable) could be characterized by socio-demographic (eg, sex, age, education level, and living situation) and clinical (eg, type of trauma, ISS, Glasgow Coma Score, being hospitalized, being treated on the intensive care unit, complications during treatment, and treated by a medical psychologist or psychiatrist), and psychological (eg, anxiety, depressive symptoms, and personality) variables (dependent variables). As a result, each class will represent a different course of ASD and PTSD. By focusing on the characteristics of the different classes, a risk profile will, consequently, be developed to determine which patients are at risk for ASD or PTSD. Sociodemographic and clinical variables are examined as moderating effect, while psychological variables are studied as mediating effects.

Linear mixed models, repeated measures, will be used to examine the effect of ASD (independent variable) on PTSD, anxiety and depressive symptoms, and QOL domains (dependent variables) over time (see Table 2).

The ISS, type of injury and type of trauma mechanism (eg, traffic accident or fall) will be used as covariates. 

**Table 2 table2:** Overview of statistical analysis

Baseline analysis and aims^a^	Independent variables	Dependent variables	Analyses
Patient characteristics	Sociodemographics	N/A^b^	Frequencies Descriptives
	Clinical variables	N/A	Frequencies Descriptives
	Psychological variables	N/A	Frequencies Descriptives
Comparison of patient characteristics	Participants versus nonparticipant	Sociodemographics Clinical variables Psychological variables	Continuous data: Independent t-test, Mann-Whitney U Categorical data: Chi-squared, Fishers’ exact test

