## Discussion

This is the first multi-method study in trauma patients that examines psychological consequences after injury, using both a qualitative focus group study design as well as an observational prospective design. In the focus group study, the aim was to interview patients about their experiences with the injury, treatment, and rehabilitation. Since it is unknown if and in what way patients’ experiences contribute to the development of psychological problems and disorders. The observational study will examine the course of ASD and PTSD, as ASD after injury is less studied and it is unknown how ASD and PTSD develop over time up to 12 months after injury. Moreover, as a result of all outcome measures, a risk profile of patients may be determined to predict which patients are at risk for developing ASD or PTSD. Altogether, this study will provide information concerning which patients to include in further research that focuses on psychological intervention.

Several factors related to the design and execution must be taken into account. First, response bias may occur in the focus group study. Patients may decline participation because they are not interested in discussing their experiences, or it might be too confronting to talk about their experiences and psychological problems. Second, it is known that the population of trauma patients has a broad variety of trauma mechanisms and injuries. Therefore, it might be difficult to generalize to the whole trauma population. However, concerning the observational study, almost all trauma patients being treated in the shock room will be included from two different Level-1 trauma centers so data saturation can be reached. These centers are located in different provinces and cities in The Netherlands. Therefore, a representative population in the observational study can be included. Third, patients with severe injuries might be less capable to complete the baseline questionnaire almost directly after injury due to being treated at the intensive care unit. Patients will, therefore, be asked to fill in the date of completing the questionnaire and if they needed any help. Then, the time between injury and measurement can be analyzed. This provides information on what time severely injured patients are capable to complete the baseline questionnaire.

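### ASD is measured once, at baseline, so the planned repeated-measures latent class analysis cannot yield a separate course of ASD; the repeated indicator must be defined

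*Protocol article*

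**What the plan says.** All places are in the Protocol article.

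- **Schedule in the text** (Methods, Data Collection, Observational Study). The general rule is "All outcome measures will be assessed after treatment in the shock room (baseline), 3, 6, 9, and 12 months after injury". The next sentence makes the exception: "However, ASD and personality will only be measured at baseline (see Table 1".
- **Schedule in Table 1.** The MINI-Plus and IES-R rows, both primary outcomes with ASD and PTSD as domains, carry the time points "Baseline 3 months 6 months 9 months 12 months". The NEO-FFI and STAI-Trait rows show baseline only. Nothing in the table limits ASD to baseline.
- **Definition** (Introduction): "ASD can only be diagnosed within the first month after trauma and last for less than a month".
- **Aim** (Introduction): "an aim of the observational study is to examine the courses of ASD and PTSD (aim 2".
- **Analysis** (Statistical Analysis, Observational Study): "Repeated measures of latent class analysis will be used to analyze the courses (ie, time is independent variable) of ASD and PTSD (dependent variables". Table 2 repeats this for aim 2, with time as the independent variable and ASD and PTSD as the dependent variables.
- **What follows from the classes.** The same section builds the aim 3 risk profile from the characteristics of the classes. The Introduction words aim 4 as the effect of the natural course of ASD symptoms. The Discussion gives 12 months as the horizon over which ASD and PTSD are to be followed.

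**The concern.** The aim, the schedule and the model are all stated in the article, and for ASD they do not fit together. A variable recorded once has no course, yet ASD is named as an outcome that changes with time.

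Table 1 does not settle the matter. It cites ASD under instruments given five times, while the text that refers to it says ASD is baseline only. Scoring ASD at the later visits would not help either, because the article's own definition rules out an ASD diagnosis at 3, 6, 9 or 12 months.

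These are the primary outcome measures, and the classes feed the risk profile. If the repeated indicator is left open, an analyst has to choose what the classes represent once the data are in. Readers could then take a class for a trajectory of ASD when it rests on one ASD measurement and four measurements of something else.

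**Working it through.** The article gives no figure on this point to reproduce. The check is a count of occasions, followed by a test of what such a count can support.

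**Step 1. Occasions on which ASD is available**

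| Source | ASD occasions |
|---|---|
| Data Collection text | 1 (baseline) |
| Table 1, MINI-Plus and IES-R rows read literally | 5 (baseline, 3, 6, 9, 12 months) |
| Introduction, first-month window applied to the five visits | at most 1 (baseline) |
| Statistical Analysis and Table 2, aim 2 | needs more than 1, since time is the independent variable |

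The first and third rows agree with each other, and both conflict with the fourth.

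**Step 2. What a latent class model can identify**

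For a binary status at T occasions and C classes, the unrestricted model has (C - 1) class proportions and C × T conditional probabilities, against 2^T - 1 free cell probabilities. Hence df = (2^T - 1) - [(C - 1) + C × T]. A negative df means the classes cannot be identified. A df of zero or more is necessary but not sufficient.

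| T | C | Free cells | Parameters | df |
|---|---|---|---|---|
| 1 | 2 | 1 | 1 + 2 = 3 | -2 |
| 1 | 3 | 1 | 2 + 3 = 5 | -4 |
| 4 | 2 | 15 | 1 + 8 = 9 | 6 |
| 4 | 3 | 15 | 2 + 12 = 14 | 1 |
| 4 | 4 | 15 | 3 + 16 = 19 | -4 |
| 5 | 2 | 31 | 1 + 10 = 11 | 20 |
| 5 | 3 | 31 | 2 + 15 = 17 | 14 |
| 5 | 4 | 31 | 3 + 20 = 23 | 8 |

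T = 1 is ASD status as the text schedules it. T = 4 is PTSD status at 3 to 12 months. T = 5 can be filled only by a measure that has meaning at every visit.

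**Step 3. Could one occasion be rescued by richer data?**

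Several dichotomous MINI-Plus items, or an IES-R score, at baseline could support classes at that one time point. Those classes would describe symptom pattern or level at baseline. They would not describe change over time, which is what aim 2 asks for.

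**Step 4. What remains estimable**

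- Courses of PTSD status over the later visits (T = 4).
- A common course of IES-R symptom severity over five visits, since the article describes the IES-R as covering severity of both ASD and PTSD.
- Aim 4 with baseline ASD as a predictor in the linear mixed models, for which one measurement is enough.
- A cross-sectional description of who has ASD at baseline, as part of aim 3.

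**The case against.** The strongest reply is that a joint course was meant: acute symptoms at baseline, PTSD symptoms afterwards, on one scale. The Introduction explains courses in terms of onset and the stability of symptom severity, the IES-R is given five times, and the Statistical Analysis section speaks of one set of classes for ASD and PTSD together. Such a course can be estimated from the scheduled data, and the df of -2 applies only to ASD status modelled on its own. This stands as a description of what is feasible. It does not remove the conflict, because the article never declares a joint course or names the IES-R score as the repeated indicator, and Table 2 lists ASD as a dependent variable over time. Detail may sit in a fuller document that is not shown, but the mismatch between the stated schedule and the stated model is in this one.

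Second, Table 1 is organised by instrument, and its domain column shows what each instrument covers. This largely stands. A reader might infer that the plan would fill the later ASD entries with structural zeros, but that happens only if the baseline-only sentence is ignored. The table is unclear rather than a separate instruction to diagnose ASD at 12 months. The extracted table may also have lost some alignment. The conflict between the text and Table 2 does not depend on it.

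Third, a reader might infer that listing PTSD at baseline is an error. The article says both instruments assess symptoms, and PTSD symptoms can be recorded at baseline even though a diagnosis needs at least a month of them.

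Fourth, a reader might infer that many late baselines would be misclassified as ASD. The article sets no latest date for baseline and approaches unconscious patients once they are lucid, but it gives no share of late baselines. It also records the completion date and says: "Then, the time between injury and measurement can be analyzed". No patient count can be attached to this. The 25-33% in the Abstract is for ASD or PTSD combined, so it does not give a number of ASD cases either.

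**Conclusion.** The point holds for a separate course of ASD. The text and the article's own definition leave at most one of five visits for ASD, while aim 2 and Table 2 require ASD to vary over time. The aim 3 risk profile is affected as far as it relies on those classes, and the wording of aim 4 shares the problem although its model does not.

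Two stronger conclusions are not supported. One is that aims 2 and 3 cannot be answered at all: PTSD courses, a common severity course and a cross-sectional account of baseline ASD are all available. The other is that the objective in the Abstract is wrong. It reads "a risk profile will be developed to determine which patients are at risk for developing ASD or PTSD during the 12 months after injury", and ASD arising in the first month falls within that wording.

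The conclusion rests on the baseline-only sentence being the intended schedule and on the first-month definition being applied as written. It uses no assumed rate. The df figures illustrate the case of a binary ASD status modelled alone, which the article does not explicitly specify.

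**What to change.** 1. Reconcile the Data Collection text with Tables 1 and 2: mark ASD as baseline only in Table 1, and remove it as a time-varying dependent variable in Table 2.
2. Define the latent class indicator as IES-R symptom severity at the five visits and/or MINI-Plus PTSD status at 3, 6, 9 and 12 months. If PTSD status is used alone, an unrestricted model on four binary occasions leaves df = 1 at three classes and is not identified at four.
3. Enter baseline MINI-Plus ASD as a predictor of class membership.
4. Word aims 2 to 4 so that ASD is a baseline state and not a 12-month course.
5. As a minor addition, use the recorded completion date to treat a baseline completed after the first month as not assessable for ASD, in line with the Introduction. The article mentions the date for the questionnaire, so the date of the MINI-Plus interview should be kept in the same way.

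The cost is rewording the aims and the two tables and stating one analysis choice. No extra visits or instruments are needed. The downside is that the study can no longer claim to describe a separate course of ASD.

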##### Acute Stress Disorder and Post Traumatic Stress Disorder

The MINI-Plus [22] and the IES-R [30] assess ASD and PTSD symptoms. Since both instruments are often used (together) in clinical practice, we will use both in the current study.

The MINI-Plus is a short structured interview based on the Diagnostic and Statistical Manual of Mental Disorders (DSM-5) and it will be used to assess ASD and PTSD symptoms [22]. The items are dichotomous because symptoms are present or absent. The DSM-5 is a classification of mental disorders with associated criteria designed to facilitate more reliable diagnoses of these disorders compared to the DSM-IV. It is a standard reference for clinical practice in the field of mental health [22]. For diagnostic criteria for ASD, see Multimedia Appendix 1 and for PTSD, see Multimedia Appendix 2.

The IES-R is a self-report questionnaire to assess symptom severity of ASD and PTSD [30]. It consists of 15 items which measure intrusive re-experiences of the injury and avoidance of injury-related stimuli. The respondent states whether the content of each statement was present during the past 7 days. A 4-point Likert scale will be used ranging from 0 (*not at all*) to 5 (*often*). The cut-off score for a probable diagnosis of PTSD is ≥ 33 and have good diagnostic accuracy [31,32]. The IES-R has good psychometric properties [32] and the Dutch translation of the IES-R has been found to be valid and reliable [33].

##### Anxiety and Depressive symptoms

The HADS measures anxiety and depressive symptoms [34]. It is a generic questionnaire measuring levels of anxiety (7 items) and depression (7 items) with a 4-point rating scale ranging from 0 (*not at all*) to 3 (*very much*). Subscale values ≥11 for one of the subgroups are observed as an indication for a psychological disorder, as this cut-off score provides the lowest proportion of false positives (5% for anxiety and 1% for depression) [34]. The questionnaire is shown to be reliable and valid [34].

**Table 1 table1:** Overview of self-report questionnaires

Study and related questionnaires		Domain	Outcome measures	Time point for retrieval
**Focus group study**				
	Patients’ experiences	N/A^a^	Primary outcome	N/A
	IES-R^b^	PTSD^c^	Secondary outcome	Shortly after meeting
	HADS^d^	Anxiety Depressive symptoms	Secondary outcome	Shortly after meeting
	Sociodemographic questions	Educational level Living situation Paid job	Secondary outcome	Shortly after meeting
**Observational study**				
	MINI-Plus	ASD^e^ PTSD	Primary outcome	Baseline 3 months 6 months 9 months 12 months
	IES-R	ASD PTSD	Primary outcome	Baseline 3 months 6 months 9 months 12 months
	HADS	Anxiety Depressive symptoms	Secondary outcome	Baseline 3 months 6 months 9 months 12 months
	NEO-FFI^f^	Personality	Secondary outcome	Baseline
	STAI^g^-Trait	Personality	Secondary outcome	Baseline
	WHOQOL-Bref^h^	QOL^i^	Secondary outcome	Baseline 3 months 6 months 9 months 12 months

^a^N/A: Not applicable.

^b^IES-R: Impact of Event Scale-Revised.

^c^PTSD: posttraumatic stress disorder.

^d^HADS: Hospital Anxiety and Depression Scale.

^e^ASD: acute stress disorder.

^f^NEO-FFI: NEO Five-Factor Inventory.

^g^STAI: State Trait Anxiety Inventory.

^h^WHOQOL-Bref: World Health Organization Quality of Life assessment instrument-Bref.

^i^QOL: quality of life.

##### Personality

Personality will be assessed using the NEO-FFI [35] and the STAI-Trait scale [36]. The 60-item NEO-FFI measures the Big Five personality domains: (1) Neuroticism, (2) Extraversion, (3) Openness to experience, (4) Agreeableness, and (5) Consciousness from the five factor model [35]. Each statement is rated on a five-point rating scale ranging from 1 (*strongly disagree*) to 5 (*strongly agree*), resulting in dimension scores between 12 and 60. The psychometrics has been extensively assessed and the internal consistency, test-retest reliability, and validity are acceptable to good [37].

The STAI (short form) consists of 20 items for measuring state anxiety (10 items) and trait anxiety (10 items) [36]. In this study, only the STAI-Trait scale will be used. This scale describes the person’s tendency to experience feelings of anxiety and stress. The STAI-Trait scale has a four-point rating scale ranging from 1 (*almost never*) to 4 (*almost always*). The Dutch version of the STAI is a reliable and valid instrument [38].

